### Assessments

A trained researcher will provide the participant with an informed consent form. The same researcher, blind to the treatment allocation, will assess all participants at two-time points: before and after the interventions. Participants will be asked not to inform the evaluators about the type of intervention they received.

### Interventions

Participants will be randomly assigned to the VRG or EG groups, with an allocation ratio of 1:1. Participants in the VRG will participate in 14 IVR training sessions lasting 45 min, twice a week. The Oculus Quest 2 Advanced 128Gb VR Headset will be used, attached, and adjusted to the participant's head. A BOBOVR M2 Pro adapter will be used for greater comfort, a support that offers greater comfort, and a magnetic battery with quick replacement and charging and two wireless handheld controllers. In each training session, participants will play three games on odd days and another three games on even days. A trained physiotherapist will accompany all sessions to correct the participants' movements and posture through manual guidance and verbal cues. The level of difficulty progression will be according to the participant's performance. Scores will be recorded for learning analyses. The time required to change the game will be approximately three minutes, and participants will sit in a chair during this period. Individuals in the EG will participate in 14 training sessions of a motor-cognitive integrated intervention, lasting 45 min and having a frequency of twice a week. A trained physiotherapist will conduct the sessions.

### Selection and description of the games

The games require the participant to remain standing and were selected based on their motor and cognitive demands. Table 1 describes the games.

**Table 1 tbl0001:** Brief description of the games. Figures resulting from the game's print screen.

### Selection and description of motor-cognitive integrated intervention

Table 2 describes the exercises of the motor-cognitive integrated intervention.

**Table 2 tbl0002:** Brief description of the exercises.

Description of Multimodal Exercises with integrated cognitive interventions	
Individually supervised interventions by a trained physical therapist. Twice a week, for 45-minutes, over 7-weeks. First day: Exercises 1, 2, 4, 6, 8, and 10. Second day: Exercises 1, 3, 5, 7, 9, and 10.	
**Description**	**Materials**
1. Walking while the participant verbalizes words with the same pre-determined phonetic initial.	None
2. During the plantar flexion movement, the individual must touch colored markers positioned on the wall in a random order pre-defined by the researcher.	Colored EVA circles
3. Execution of a circuit consisting of activities using proprioceptive discs and unstable surfaces, combined with simple mathematical calculations.	Proprioceptive disc and 6 mats (55 × 95 × 3 cm)
4. Performing ball-throwing exercises while the participant verbalizes words belonging to specific semantic categories.	Inflatable ball (20 cm)
5. Performing exercises on a step platform with load, alternating legs according to pre-defined instructions.	Step platform (60 × 28 × 10 cm)
6.Memorizing the stacking order of cones on a chair and replicating this order on another chair positioned 3 m away.	6 colored cones and 2 chairs
7. Maintaining static balance on an unstable surface while the participant claps upon hearing a specific letter of the alphabet announced by the researcher.	3 mats (55 × 95 × 3 cm)
8. Hip adduction exercise with a ball between the knees and hip abduction against elastic resistance around the knees, while the participant recalls and describes figures from a previously presented image.	Inflatable ball (20 cm), elastic band, and printed images
9. Walking with arms extended while holding a ball, performing upper limb abduction movements according to opposite verbal commands.	Inflatable ball (20 cm)
10. Stretching.	None

Physiotherapists and neuropsychologists mutually agreed to select the exercises and games according to the specific demands. The cognitive and motor demands of the games and exercises were then paralleled, illustrated in Fig. 1, Fig. 2.

**Fig. 1 fig0001:**
[figure not shown]
Cognitive domains are stimulated during exercises and games.

**Fig. 2 fig0002:**
[figure not shown]
Motor skills stimulated during exercises and games.

### Outcome measures of acceptability

Feasibility will be assessed by the participant's game performance, measured by the scores achieved. Increasing scores indicate that the participant can play and improve their performance in the games. It is the primary measure of the game that promotes motivation.^26^ Acceptability will be evaluated through a game satisfaction questionnaire. The questionnaire consists of nine questions, including participants' perceptions of the games (“What did you think of the game?”; “Would you recommend this game?”; “Would you play this game at home?").

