### Hypotheses

1.VR interventions will significantly improve postural control, gait, functionality, cognition, and mood more than the motor-cognitive integrated intervention.2.The authors hypothesize that participants undergoing VR interventions will improve their performance in the games.3.The authors expect that commercial VR games will be acceptable to older adults with mild NCD or mild major NCD. Although this population may not be familiar with this technology, commercial games were developed for entertainment in an attractive and motivating virtual environment and were easy to use.

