#### Exclusion criteria

Participants who experience cybersickness during the familiarization session and those who miss the first two consecutive sessions will be excluded. Additionally, participants must complete 100 % of the training sessions to remain in the study. They may miss up to 20 % of the sessions, provided that all missed sessions are made up through compensatory sessions, to be scheduled in agreement with the research team.

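### Rising game scores are read as feasibility and improvement, but difficulty follows performance and non-completers are removed, so the score trend is ambiguous and selective

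*Protocol article*

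**What the plan says.** Under Outcome measures of acceptability, the protocol article ties feasibility to the games themselves: "Feasibility will be assessed by the participant's game performance, measured by the scores achieved". It then fixes the interpretation: "Increasing scores indicate that the participant can play and improve their performance in the games". Acceptability is a separate outcome, measured by a nine-question satisfaction questionnaire.

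Under Interventions, difficulty is not held constant: "The level of difficulty progression will be according to the participant's performance". The same scores have a second use: "Scores will be recorded for learning analyses". The games alternate, in that "participants will play three games on odd days and another three games on even days".

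Hypothesis 2 states that "participants undergoing VR interventions will improve their performance in the games". The scores are the only measure of game performance described.

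Under Exclusion criteria, participants are excluded for cybersickness at familiarization or for missing the first two consecutive sessions. All others must complete 100% "of the training sessions to remain in the study", with any missed sessions made up.

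**The concern.** Difficulty moves in response to the ability that the score is meant to reveal. Scores from different sessions may therefore come from different tasks. A participant who learns and is moved up may show a flat or falling score, and the stated reading rule would then find no improvement. The test of Hypothesis 2 would depend partly on when levels changed.

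The second issue is who supplies the scores. The exclusion criteria remove people who do not tolerate the headset or do not complete the sessions, and these are the people a feasibility outcome most needs to count. Dissemination policies describes the project as preliminary work for a later definitive trial. That trial will need retention, attendance and intolerance figures, and a score trend does not supply them.

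**Working it through.** The plan states no figure on this point, so there is none to reproduce. The check sets the sections side by side and then sizes the effect under stated assumptions.

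**From the document**
- 14 sessions, with two sets of three games alternating: 14 / 2 = about 7 plays per game, or 6 steps from first to last play.
- Difficulty follows performance (Interventions), while rising scores are read as improvement (Outcome measures of acceptability).
- The visible text does not say that scores are taken at a fixed level, adjusted for level, or analysed with the level reached. It names no score or trend that would count as not feasible.

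**Ratio of last to first score (assumed inputs)**

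Let ability raise the score by 10% per play, and let each level rise multiply the score by (1 − c). With m level rises, the ratio is 1.1^6 × (1 − c)^m.

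| Level rises m | Cut per rise c | Last / first |
|---|---|---|
| 0 | – | 1.1^6 = 1.77 |
| 1 | 10% | 1.772 × 0.90 = 1.59 |
| 1 | 25% | 1.772 × 0.75 = 1.33 |
| 2 | 10% | 1.772 × 0.81 = 1.43 |
| 2 | 25% | 1.772 × 0.5625 = 1.00 |

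The same 77% gain in ability appears as anything from 77% down to nothing. In most rows the trend still rises; it disappears only at the severe end of this range.

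**Chance that one participant's fitted slope is positive (assumed inputs)**

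Take 7 plays at t = 0 to 6, a true gain of 0.2 per play, noise SD 0.5, and difficulty that absorbs a fraction k of the gain. If the score gives no credit for level, the expected slope is 0.2 × (1 − k). Its standard error is 0.5 / √Σ(t − 3)² = 0.5 / √28 = 0.0945. Then P(slope > 0) = Φ(expected slope / 0.0945).

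| k | Expected slope | P(slope > 0) |
|---|---|---|
| 0 | 0.20 | 0.98 |
| 0.5 | 0.10 | 0.86 |
| 1 | 0.00 | 0.50 |
| 1.5 | −0.10 | 0.14 |

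A simulation with 5,000 repetitions per setting gave the same values. Two further results matter:
- If the score fully credits level, the slope stays at about 0.20 and the probability at about 0.98 for every k. The scoring rule therefore decides whether there is a problem.
- With no true gain, a rising level without credit pushes the slope down (−0.10 at k = 0.5, −0.20 at k = 1). Under these rules the level schedule hides learning; it does not manufacture it.

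**Selection**

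Exclusion at familiarization, exclusion for missing the first two consecutive sessions and the completion requirement all act on tolerance or adherence. Anyone removed contributes either no trend or a shortened one. Table 4 does not place the familiarization session, so it is not visible whether those exclusions come before or after allocation.

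**The case against.** The strongest reply is that the scoring rule is unknown. The article speaks of scores achieved and does not call them raw. Table 1 describes the games, but its content is not readable in the text reviewed here and may give the rule. If the games award more points at harder levels, the trend can track improvement. This stands, so the point has to be conditional. A reader might infer that the trend does not measure improvement at all, and the document does not support that.

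A reader might also infer that scores cannot show infeasibility. That goes too far: absent or very low scores could show inability to play. What is unclear is the meaning of a flat or falling trend when no criterion is stated.

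Nor does the text say that scores exist only for completers. Someone who leaves midway has already produced scores, and the article does not say that these are discarded. The supportable statement is that the least tolerant participants may be under-represented.

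It is tempting to add that the level schedule could falsely confirm Hypothesis 2, for example when someone stays at an easy level and scores higher. That is real improvement at a matched level. If harder levels lower scores, the bias is mainly against the hypothesis.

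Finally, this is a condensed article. Level may be logged, and how the learning analyses use it may be set out elsewhere. Attendance and cybersickness must be tracked for the exclusion criteria to operate, and adverse events are recorded. All of this is fair, and it makes the remedy easy. It does not remove the conflict, because the article states an inference rule in one section and undermines it in another.

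**Conclusion.** The concern holds in conditional form. Unless a game's score credits level, the trend over about 7 plays is confounded with difficulty, and a flat or falling trend cannot separate absence of learning from learning met by a harder level. Under the assumed 10% gain per play and two level rises each cutting the score by 10% to 25%, the last-to-first ratio is 1.43 to 1.00, against 1.77 at fixed difficulty. Only the 7 plays come from the document; the gain, the cuts and the number of level rises are assumptions.

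Separately, and under any scoring rule, the exclusion criteria make a score trend a selective measure of feasibility. The document gives no figure for the size of this effect.

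The effect is confined to the feasibility conclusion and Hypothesis 2. The between-group comparison of the clinical outcomes in Table 3 is untouched.

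**What to change.** - Log the level with every score, and state for each game whether its score credits level.
- Test Hypothesis 2 on scores at a matched level early and late in training, or with a mixed model of score on exposure number adjusting for level. Where a participant has no level common to early and late plays, only the model is available. Report the highest level reached.
- Qualify the sentence on increasing scores so that it refers to scores at a comparable level, and keep scores as a learning outcome.
- Report feasibility as retention, sessions attended without make-up, and cybersickness or withdrawal, with everyone allocated to VR as the denominator. Count exclusions at familiarization separately.

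None of this changes how difficulty is set or who is treated. The cost is one extra field in the score log and some plan wording; the feasibility data are already needed to apply the exclusion criteria. Trial status reports about 50% recruited, so the change would serve the remaining participants. Sessions already run without a recorded level may be usable only descriptively.

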### Clinical outcome measures

Table 3 shows the assessments used as Clinical Outcome Measures.

**Table 3 tbl0003:** Clinical outcome measures and assessments.

Clinical outcome	Assessment
Postural control	Mini-BESTest^27^
Gait	Dynamic Gait Index^28^
Cognitive functions	Neurocognitive Battery of SGHC-FMUSP; Word Accentuation Test^29^; MoCA (Montreal Cognitive Assessment)^30^
Functionality	Functional Activities Questionnaire^31^
Mood	Generalized Anxiety Disorder 7-item^32^; Patient Health Questionnaire-9^33^
Manual dexterity	Box and Blocks^34^
Strength	Hand Grip Test^35^

### Participant timeline

Table 4 illustrates the study participant enrollment process, intervention, and timing of assessments.

**Table 4 tbl0004:** Activity timeline.

	Day 1	Day 2	Days 3‒16	Day 17
Eligibility screening	x			
Initial neuropsychological assessments	x			
Informed consent	x			
Initial physical assessments		x		
Allocation Interventions		x		
			x	
Final neuropsychological assessments				x
Final physical assessments				x

### Sample size

The sample size calculation was based on a review with meta-analysis regarding the effectiveness of VR for individuals with mild cognitive impairment or dementia, which produced small to medium effect sizes using a random effects model (effect size = 0.29) from a total of 11 studies.^36^ Assuming a dropout rate of 20 %, a total sample size of 32 participants (16 per treatment group) would provide a power of 0.8 with a two-tailed α error of 0.05.

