### Randomization

Participants will be randomly assigned to the VRG and EG with a 1:1 allocation ratio. A researcher not involved in the study will prepare the randomization schedule from a computer-generated list of random numbers.

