### Dissemination policies

The dissemination will aim to inform a wide range of local, national, and international audiences about the results and conclusions. However, it should be remembered as part of this strategy that the current project is a preliminary work intended to inform a subsequent definitive clinical trial. The goal is to publish the present research in journals that cover relevant medical specialties, preferably those that deposit publications in open-access databases to enhance free dissemination. Additionally, the authors aim to present this research at appropriate national and international conferences.

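### The stated power of 0.8 at effect size 0.29 does not hold: with 20% dropout, 32 participants give roughly 11–17%, and the sample size fits a difference up to about four times larger

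*Protocol article*

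**What the plan says.** The Sample size section bases the calculation on a meta-analysis of virtual reality in cognitive impairment or dementia, "which produced small to medium effect sizes using a random effects model (effect size = 0.29) from a total of 11 studies". It allows for 20% dropout and concludes that "a total sample size of 32 participants (16 per treatment group) would provide a power of 0.8" with a two-tailed error of 0.05. It does not name the effect-size metric, the test, the outcome or a pre-post correlation.

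The comparison to be powered is in Hypotheses, item 1: "VR interventions will significantly improve postural control, gait, functionality, cognition, and mood more than the motor-cognitive integrated intervention". The comparator is active, allocation is 1:1, and Study design gives two assessments, before and after. Data analysis plans a repeated-measures general linear model and a univariate one. Dissemination policies adds that "the current project is a preliminary work intended to inform a subsequent definitive clinical trial".

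**The concern.** A standardised difference of 0.29 normally needs well over 100 participants per arm, so 80% power from 16 per arm is not credible at first sight. The calculation is the only justification given for the sample size.

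If the claim is wrong, the trial cannot test Hypothesis 1 at the effect it plans for. If the assumed benefit is exactly true, most such trials would still end non-significant, and a reader who trusts the 0.8 figure could take that as evidence that the interventions do not differ. The reverse risk also matters. In so small a trial, an estimate must be far above 0.29 SD to reach significance, so a positive result would give an inflated figure to the later definitive trial.

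**Working it through.** **Inputs from the protocol article.** Effect size 0.29, two-sided α 0.05, claimed power 0.8, N = 32 (16 per arm), dropout 20% (Sample size); 1:1 allocation (Randomization); two assessments (Study design). Completers: 16 × 0.8 = 12.8, about 13 per arm, 26 in total.

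**Assumption.** The pre-post correlation r is not given. I use 0.5 to 0.7 as the main range and go up to 0.9 as a stress test.

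**1. Reproducing the plan's figure.** I found one route to 32: enter 0.29 as Cohen's f for the group-by-time interaction, with 2 groups, m = 2 measurements and r = 0.5.

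- λ = f² × N × m / (1 − r), with an F test on 1 and N − 2 degrees of freedom.
- N = 24: λ = 0.0841 × 24 × 2 / 0.5 = 8.07, power 0.775.
- N = 26: λ = 0.0841 × 26 × 2 / 0.5 = 8.75, power 0.810. This is the smallest even N that reaches 0.8.
- Dropout: 26 × 1.2 = 31.2, rounded up to 32 for equal arms.

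In a 2 × 2 design the interaction effect in each cell is one quarter of the between-group difference in change, so that difference is 4f = 4 × 0.29 = **1.16 SD**.

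**2. Power at a between-group difference of 0.29 SD.** Noncentral t, with noncentrality (0.29 / s) × √(n/2), where n is the number per arm and s is the residual SD in units of the outcome SD:

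- post-score: s = 1
- change score: s = √(2(1 − r))
- ANCOVA: s = √(1 − r²), with one degree of freedom fewer

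Example, post-score with n = 13: 0.29 × √6.5 = 0.739, 24 degrees of freedom, power 10.9%.

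| Analysis | r | 13 per arm | 16 per arm |
|---|---|---|---|
| Post-score | – | 10.9% | 12.5% |
| Change score | 0.5 | 10.9% | 12.5% |
| Change score | 0.7 | 15.0% | 17.6% |
| ANCOVA | 0.5 | 13.0% | 15.0% |
| ANCOVA | 0.7 | 16.8% | 19.9% |
| ANCOVA | 0.8 | 21.9% | 26.2% |
| ANCOVA | 0.9 | 36.9% | 44.4% |

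As a cross-check, 0.29 SD on the interaction scale is f = 0.29 / 4 = 0.0725. At N = 26 and r = 0.5 this gives λ = 0.547 and power 10.9%, the same as the change-score row. Using f = d/2 = 0.145 gives 29% at N = 26 and 36% at N = 32, but on this scale 0.145 already stands for 4 × 0.145 = 0.58 SD, so those values flatter the design.

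**3. Size needed for 80% power at 0.29 SD.** Post-score: 188 completers per arm, so 376 / 0.8 = 470 randomised. ANCOVA at r = 0.7: 97 completers per arm. ANCOVA at r = 0.8: 69 per arm.

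**4. What 26 completers can detect (80% power) and estimate (95% CI half-width = t × s × √(2/13)).**

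| Analysis | r | Detectable difference | Multiple of 0.29 | CI half-width |
|---|---|---|---|---|
| Change score | 0.5 | 1.15 SD | 3.9 | 0.81 SD |
| Change score | 0.7 | 0.89 SD | 3.1 | 0.63 SD |
| ANCOVA | 0.5 | 0.99 SD | 3.4 | 0.70 SD |
| ANCOVA | 0.7 | 0.82 SD | 2.8 | 0.58 SD |

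The half-width is also the smallest estimate that reaches significance: 0.58 / 0.29 = 2.0 to 0.81 / 0.29 = 2.8 times the planned effect.

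**The case against.** The strongest reply is that the metric is unnamed. If 0.29 was meant as Cohen's f, the calculation was carried out correctly and matches the planned repeated-measures model. The figure is indeed not a slip of arithmetic, and how it arose is inference. But the section describes its source as one "which produced small to medium effect sizes using a random effects model". On the usual benchmarks 0.29 is small to medium as a standardised mean difference (0.2 to 0.5) and above medium as f (0.25). Read as f, the plan would expect about 1.16 SD over an active comparator, which contradicts that description. Either reading requires a correction.

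Second, the results depend on r and on the analysis. This stands. The range of 11–17% is for 26 completers and r up to 0.7; with higher r or no dropout, power rises. The factor of four applies at r = 0.5 and falls to about three at r = 0.7. ANCOVA is not explicitly planned, so its rows are the favourable end. None of this comes near 0.8.

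Third, a preliminary trial may report a power calculation, and Data analysis already promises effect sizes with 95% confidence intervals. Both are fair. Calling the project preliminary is not itself an error, and part of the remedy is already in the plan. What cannot stay is a power figure that its own inputs do not support.

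**Conclusion.** The concern holds. With 0.29 as a between-group standardised mean difference, power is about 11–17% with 26 completers (change score or ANCOVA, r 0.5 to 0.7), 12.5% unadjusted with all 32 analysed, and at most about 44% under the most favourable case tried. If the assumed benefit is true, a non-significant result has a probability of about 83–89%. The trial has 80% power only for differences of about 0.8 to 1.15 SD.

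This rests on the metric implied by the document's own description and on assumed correlations. The conclusion does not change anywhere in the range examined. That 0.29 was entered as f is the probable explanation, but the conclusion does not depend on it.

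**What to change.** Keep 32 participants and replace the power sentence. Name the metric, test, outcome and correlation. Suggested text, with its correlations marked as assumptions:

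> With about 26 analysed participants, and assuming a pre-post correlation of 0.5 to 0.7, the trial has 80% power (two-sided 5%) for a between-group difference of 1.15 to 0.89 SD using change scores, or 0.99 to 0.82 SD using baseline-adjusted ANCOVA. Power at 0.29 SD is 11–15% and 13–17% respectively. The trial is preliminary. Results will be reported as estimates with 95% confidence intervals (expected half-width about 0.6 to 0.8 SD) to inform the definitive trial, and a non-significant difference will be reported as inconclusive.

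If the sponsor did intend f = 0.29, the section should say so, state that this means about 1.16 SD at r = 0.5, and justify a difference of that size against an active comparator.

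Softening Hypothesis 1 from an expected significant superiority to an estimated difference would fit the preliminary aim. It is advisable but not needed to correct the power statement.

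The cost is a wording amendment or registry note and a much less favourable stated power. With about half the participants recruited (Trial status), it can be made before results are known.
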